### Data collection and management

This study will collect the patient’s name, age, gender, diagnosis of primary tumor, location and number of vertebral metastases, pain score and imaging findings. The above information will be recorded in a unique case report for each patient. These data will be input and saved in the electronic data management system established by Mianyang Central Hospital. The final data will be reviewed, locked and used for final data analysis by key researchers and statistical analysts.

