### Measurement of the primary and secondary endpoints

Pain relief will be assessed by patients using the numerical rating scale before radiotherapy, two weeks, three months, six months and every six months after radiotherapy. The pain relief rate is the primary endpoint of this study. The secondary endpoint was a follow-up on the occurrence of side effects and the positive results of imaging, such as radiation spinal cord injury and pathological fracture. The vertebral bodies will be scanned with CT to identify radiogenic injury of the spinal cord and vertebral compression fracture.

Adverse events are being recorded in accordance with the requirements of the MedDRA. The classification of side effects was based on the CTCAE of National Cancer Institute.

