### Statistical analysis and randomization

We estimated the sample size based on paper of Fleiss, JL et al. [7]. We performed non-inferiority and equivalence trials with α = 0.025, 1-β = 0.8 and non-inferiority *Δ* = -0.15 using Pearson*X*^2^test, power = 0.809, *H*0: πt—πc ≤ -0.15, *H*1: πt—πc > -0.15.We estimate a loss to follow-up rate of 10% and the resultant required number of patients was 66. The rate of pain relief in patients with vertebral metastases receiving radiotherapy will be measured according to the results of previous trials including that by Howell et al. [8]. Randomization will be administered centrally by the SPSS24.0 software at Mianyang central hospital. Patients who meet the inclusion criteria will be randomized on a1:1 basis to one of the 2 groups. The randomization will conduct by Mianyang Central Hospital through spss24.0 software. Patients who meet the enrollment conditions will enter the control group and the study group in a ratio of 1:1.

The number, proportion and 95% confidence interval of patients with pain relief will be reported. The related toxicity will analyze by Fisher exact test.

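### The only methods the article names for the primary endpoint are unadjusted; prespecifying adjustment for pre-treatment pain score would be a small, nearly free gain in efficiency

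*Protocol article*

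**What the plan says.** All places are in the protocol article.

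- **Data collection and management** lists among the recorded items "diagnosis of primary tumor, location and number of vertebral metastases, pain score and imaging findings".
- **Measurement of the primary and secondary endpoints** fixes a pre-treatment pain measurement: "Pain relief will be assessed by patients using the numerical rating scale before radiotherapy".
- **Statistical analysis and randomization** sizes the trial for non-inferiority on the difference in relief rates with a margin of -0.15: "We performed non-inferiority and equivalence trials with α = 0.025, 1-β = 0.8", "using Pearson*X*^2^test". For the result it says "The number, proportion and 95% confidence interval of patients with pain relief will be reported". Allocation is given as "Patients who meet the inclusion criteria will be randomized on a1:1 basis to one of the 2 groups", with no stratification factor named.

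The section mentions no covariate for the primary endpoint and rules none out.

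**The concern.** The primary conclusion rests on where a confidence limit falls relative to a fixed 15-point margin, in a trial with about 30 evaluable patients per arm. A baseline measurement of the same scale that defines the outcome will be available, and the named methods do not use it. If baseline pain predicts relief, part of the variance of the crude difference comes from chance differences in baseline pain between the arms. Adjustment can remove that part without more patients or more data. The covariate has to be fixed in advance, because one chosen after outcomes are seen would be open to challenge in a non-inferiority claim.

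**Working it through.** **Inputs from the article.** One-sided alpha 0.025, margin -0.15, stated power 0.809, loss to follow-up 10%, total 66, allocation 1:1. **Assumed, because the article gives no figure:** the true relief rate (0.60 to 0.90, equal in both arms) and the prognostic strength of baseline NRS (odds ratio 1 to 2.5 per SD).

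**1. Evaluable patients.** 66 × 0.9 = 59.4, about 30 per arm. The 66 is consistent with 60 × 1.1 = 66; dividing instead, 60 / 0.9 = 66.7, gives 67. The 0.809 cannot be reproduced, because no relief rate is stated.

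**2. Crude precision.** SE = sqrt(2p(1−p)/30), half-width = 1.96 × SE, power = Φ(0.15/SE − 1.96).

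| p | SE | Half-width | Power |
|---|---|---|---|
| 0.70 | 0.1183 | 0.232 | 24% |
| 0.80 | 0.1033 | 0.202 | 31% |
| 0.90 | 0.0775 | 0.152 | 49% |

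**3. Chance imbalance.** The difference in mean baseline score has standard error sqrt(2/30) = 0.258 SD. P(|difference| ≥ 0.5 SD) = 2(1 − Φ(0.5/0.258)) = 0.053. For 0.3 SD it is 0.245.

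**4. Effect of a 0.5 SD imbalance at an odds ratio of 2 per SD.** Place the arm means 0.25 SD above and below the overall mean and average the logistic response over a normal covariate. The crude difference moves by 0.075, 0.066 and 0.052 at p = 0.60, 0.70 and 0.80. Divided by 0.15, these are 0.50, 0.44 and 0.35 of the margin.

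**5. This shift is already inside the crude interval.** At p = 0.70, a shift of 0.066 is 0.066/0.1183 = 0.56 SE, and it needs an imbalance of 0.5/0.258 = 1.94 standard errors. The share of crude variance due to baseline imbalance is therefore about (0.56/1.94)² = 0.08, or 8%. That is the most that adjustment could remove at this strength, before the cost of estimating the extra coefficient.

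**6. Simulation.** Several thousand trials per setting, 30 per arm, equal rates of 0.60 to 0.80, logistic model with arm and one normal covariate, standardised to a risk difference.

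| Odds ratio per SD | Variance, adjusted / crude | Change in variance |
|---|---|---|
| 1 (not prognostic) | about 1.02 | +2% |
| 1.5 | 0.97–1.00 | 0 to −3% |
| 2 | 0.92–0.95 | −5 to −8% |
| 2.5 | 0.87–0.90 | −10 to −13% |

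Type I error at the margin stayed near 0.025–0.03. With a robust standard error the power gain was at most about 2 points.

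**7. Effect on the interval.** A 10% variance cut multiplies the half-width by sqrt(0.9) = 0.949: 0.232 becomes 0.220 at p = 0.70, and 0.202 becomes 0.192 at p = 0.80. By the formula in step 2, power goes from 24% to 27% and from 31% to 33%. This ignores the cost of estimating the adjustment, so it is slightly optimistic.

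**The case against.** The strongest reply is that nothing is wrong here. A journal article condenses the protocol, and covariates for the primary model are normally left to the statistical analysis plan, which is not shown. The sentence about number, proportion and interval concerns reporting. The Pearson test appears in the sample-size statement, where an unadjusted formula is usual even if the final analysis is adjusted. Under randomisation the crude difference is unbiased and its interval has the right coverage on average. All of this stands, and it limits the point to an efficiency suggestion.

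It also rules out several stronger readings that a reader might infer:

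- **That baseline data enter no analysis.** The article does not say so. It only names unadjusted methods and is silent on adjustment.
- **That chance imbalance leaves the result biased or unprotected.** Step 5 shows that the shift is part of ordinary sampling error. The 5 to 7.5 point figure is conditional on an imbalance that about 5% of trials would see.
- **That baseline pain is the strongest predictor of relief.** The documents give no support for this. The article does not define a responder, so neither the direction nor the strength of the association can be derived from it.
- **That adjustment would repair the power.** At equal rates of 0.70 to 0.80 the trial stays far below 80% either way. Nor does this show the stated 0.809 to be wrong: equal rates near 0.956, or 0.75 against 0.88, would give it, and the article states neither.

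What survives is that a better method than those named is available, uses data already collected and keeps the margin on the same scale.

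**Conclusion.** The point holds as a minor, optional improvement. The named methods for pain relief are unadjusted, a pre-treatment NRS score will be held, and no stratification is described. Adjusting for that score would reduce the variance of the risk difference by about 0–3%, 5–8% or 10–13% at odds ratios of 1.5, 2 or 2.5 per SD, against a penalty of about 2% if the score is not prognostic. These figures assume 30 evaluable per arm, equal true relief rates of 0.60 to 0.80 and a roughly normal baseline score. The prognostic strengths are assumptions. If the unseen analysis plan already prespecifies such an adjustment, the point is met.

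**What to change.** Unless the statistical analysis plan already does so, add wording to this effect before any outcomes are seen:

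- The primary estimate is the difference in pain relief rates, study minus control, from a logistic model with arm and baseline NRS, standardised by averaging the predicted probabilities over all patients.
- Its two-sided 95% confidence interval uses a robust delta-method standard error or the bootstrap. Non-inferiority is concluded if the lower limit lies above -0.15.
- The crude difference with its 95% interval is a sensitivity analysis.

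Keep to this one covariate. At a relief rate of 80% there would be about 30 × 0.2 = 6 non-responders per arm, and at 90% about 3. A second covariate admitted only if event numbers allow would make the primary model depend on the outcomes.

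The cost is a few lines of analysis text and a little programming, with no new data and no extra patients. The responder definition and primary time point must be settled before the model can be fixed.

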**Methods:**

This study aims to verify whether reducing the radiotherapy range for vertebral metastases can achieve the same effect as whole vertebral radiotherapy while minimizing side effects. Sixty-six patients with pain caused by vertebral metastasis were randomly divided into two groups. The study group is receiving partial vertebrae body radiotherapy at the regions of abnormal signal, suspected invasion, and adjacent subclinical focus of vertebral metastasis, and the control group is receiving the same dose of radiotherapy on whole vertebrae body where metastasis occurred. After radiotherapy, along-term follow-up of patients will determine pain relief and side effects.

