**Fig. 1 Fig1:**
[figure not shown]
The International Spine Radiosurgery Consortium proposed to divide each vertebral body into 6 sectors: Sector 1 represents the vertebral body, sector 2 represents the left pedicle, sector3 represents the left transverse process and lamina, sector 4represents the spinous process, sector 5 represents the right transverse process and lamina, and sector 6 represents the right pedicle

At present, there is a single-center phase II prospective cohort study comparing the effect on pain control of conventional radiotherapy and SBRT in patients with spinal metastasis. In both treatment groups, patients had a comparable decrease in pain and analgesic use in the 3 months following treatment [2, 5]. However, there have no randomized controlled trials comparing the effect of local irradiation and whole vertebral irradiation on pain control in IMRT [6]. Therefore, we designed a randomized controlled trial to evaluate if irradiation of local metastases in the vertebral body as well as whole vertebral body irradiation can effectively control pain. We also investigated if side effects such as twinkling bone pain, spinal cord radiation injury, vertebral compression fracture, and nerve root compression were reduced.

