### Objectives

The primary endpoint is pain relief rate. The secondary endpoints are the incidence and types of side effects.

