## Discussion

Approximately one-third of patients with advanced malignant tumors will experience bone metastasis, and the spine is the most common bone metastasis, especially the lumbar spine and thoracic [9, 10]. Patients with bone metastasis often present with severe pain that is difficult to control. Some patients with vertebral metastasis even have pathological fractures and spinal cord compression. Radiotherapy is an effective treatment for alleviating the symptoms of bone metastasis [11–13].

The 2017 ASTRO update on palliative radiotherapy for bone metastases continues to recommend that patients with bone metastases can be selectively treated with 8 Gy/1 f, 20 Gy/5 f, 2 Gy/6 f, or 30 Gy/10 f with four different fractionation methods [14–16]. The 30 Gy/10 f and 8 Gy/1 f doses are widely used in conventional radiotherapy. Existing research has shown that the effects on pain relief of single radiotherapy and fractional radiotherapy are similar [11, 15–18]. However, Rades et al. showed that the recurrence of pain caused by vertebral metastases treated with large fractionation therapy could be as high as 26%, compared with conventional long-term treatment with 30 Gy/10 f, which showed better local control [19]. This is the basis for the selection of 30 Gy/10 F fractionated irradiation in our trial. We suspect that the reason for the difference in pain control and duration of pain relief may be related to the dose limitation of spinal nerves in patients with vertebral metastases. Therefore, current research on radiotherapy of vertebral metastases focuses on increasing the radiation dose without increasing the side effects to achieve better pain control [20].

According tothe2012 ISRC consensus guidelines on the target volume of spinal SRS, unless the spinous processes, lamina / bilateral pedicle and vertebral body are affected or there are extensive metastatic diseases around the epidural space, the circumferential TVs around the spinal cord should not be used. The guidelines emphasized that published guidelines on indications and practice patterns for spinal SRS are limited and there is no consensus on the definition of target volume [2]. We propose a safe and effective reduction of the target area in IGRT radiotherapy, which can effectively avoid the excessive irradiation of nerve, spinal cord and other normal tissues, and correspondingly improve the target dose setting.

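### The only between-arm safety test is limited to related toxicity, which is narrower than the side-effect endpoint and can make local irradiation look safer than it is

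*Protocol article*

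**What the plan says.** The analysis is fixed in one sentence of Statistical analysis and randomization: "The related toxicity will analyze by Fisher exact test". The term *related* is not explained there.

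The endpoint is set out elsewhere in wider terms:

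- Objectives: "The secondary endpoints are the incidence and types of side effects", with no condition on cause.
- Measurement of the primary and secondary endpoints: side effects together with "positive results of imaging, such as radiation spinal cord injury and pathological fracture".
- The same section, on ascertainment: "The vertebral bodies will be scanned with CT to identify radiogenic injury of the spinal cord and vertebral compression fracture".
- The same section, on recording: "Adverse events are being recorded in accordance with the requirements of the MedDRA". This is not limited to related events.
- Background, last paragraph, on the aim: whether "side effects such as twinkling bone pain, spinal cord radiation injury, vertebral compression fracture, and nerve root compression were reduced".

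On cause, the Background names pathological fracture and spinal cord compression as consequences of too much dose or too large an irradiated range. The Discussion assigns the same events to the disease: "Some patients with vertebral metastasis even have pathological fractures and spinal cord compression".

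**The concern.** The two arms receive the same dose and fractionation and differ in the volume treated. A smaller volume could plausibly lower radiation-caused events. It could also raise tumour-caused events in the part of the vertebra that is spared. The Background itself says that adjacent marrow spaces may harbour subclinical disease and become sites of recurrence. A test limited to events judged related keeps the harm that may fall and can drop the harm that may rise.

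Randomisation protects a comparison of all events by arm. It does not protect a comparison filtered by a judgment of cause made after treatment, least all where one outcome, such as a fractured vertebra, has two possible causes and the intervention may shift the balance between them.

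Fewer side effects is half of the expected conclusion in the Abstract. The Discussion plans to raise the dose to the reduced target if pain relief proves equivalent. A safety comparison that is too favourable would be carried into that step.

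**Working it through.** **1. Scope of the endpoint against scope of the test.**

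| Event | Named as an outcome? | Tied to radiation in the text? |
|---|---|---|
| Vertebral or pathological fracture | Yes (Background; Measurement section) | Not clearly; in the CT sentence the adjective may or may not extend to fracture |
| Nerve root compression | Yes (Background) | No |
| Spinal cord injury from radiation | Yes (Background; Measurement section) | Yes |
| Spinal cord compression from tumour | No | Not applicable |
| Toxicity entering the Fisher test | Related toxicity only | Undefined |

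The last row is narrower than the endpoint on the ordinary reading of *related*. For the cord, the narrowing does not depend on that word, because only radiation injury is named. The Inclusion criteria require that no tumour tissue compresses the cord at entry, so tumour-driven compression seen later would be a new event on study.

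**2. What the restriction can do to the estimate.** The article states no toxicity rates and no figure for this comparison, so there is nothing of its own to reproduce. Its total of 66 and power of 0.809 belong to the pain-relief test. I use 66 only for arm size: 66/2 = 33 per arm randomised, and 66 × 0.9 = 59.4, about 30 per arm after the stated 10% loss.

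Let r be the risk of an event judged related and u the risk of an event judged unrelated, with each patient counted once. Then

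any-cause difference = (r_study − r_control) + (u_study − u_control).

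The related-only analysis reports the first bracket. The second bracket is what it leaves out.

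**3. Assumed rates.** Take r_study = 5% and r_control = 10%, 15% or 20%. Take u_control = 0 and u_study = 0, 5% or 10%. Differences are study minus control, in percentage points; negative favours local irradiation.

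| Related, study vs control | Related-only difference | Any cause, excess 0 | Any cause, excess 5 | Any cause, excess 10 |
|---|---|---|---|---|
| 5% vs 10% | −5 | −5 | 0 | +5 |
| 5% vs 15% | −10 | −10 | −5 | 0 |
| 5% vs 20% | −15 | −15 | −10 | −5 |

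For example, in the second row with an excess of 10: (5 − 15) + (10 − 0) = 0. In 33 patients per arm the related-only analysis would expect 33 × 0.05 = 1.65 against 33 × 0.15 = 4.95 events. The any-cause analysis would expect 4.95 in each arm.

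**4. Chance of a significant result.** Exact power of the two-sided Fisher test at 0.05 for the related-only comparison, with 30 and 33 per arm:

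- 5% vs 10%: 1.9% and 2.5%
- 5% vs 15%: 9.3% and 11.9%
- 5% vs 20%: 24.1% and 29.3%

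Under these rates the test would seldom be significant. The distortion would show mainly in the reported counts and proportions.

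**The case against.** A reader might infer three stronger things, none of which the article supports.

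- *That tumour-caused fractures and compressions are classed as unrelated.* No sentence classes any event that way or gives a rule for cause. Fracture and nerve root compression are listed without a clear causal condition, adverse events are recorded without one, and *related toxicity* may simply mean the toxicity belonging to the secondary endpoint just described.
- *That tumour is left unirradiated in the study arm.* The Abstract describes that arm as receiving "partial vertebrae body radiotherapy at the regions of abnormal signal, suspected invasion, and adjacent subclinical focus of vertebral metastasis". Known and suspected disease is treated in both arms at the same dose. Only sectors beyond that are spared, so a rise in tumour-driven events is a possibility, not an expectation.
- *That the treating clinicians attribute cause.* The article names neither an attribution step nor an assessor.

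It is also fair that a condensed article may leave the definition of *related* to the full protocol or analysis plan. Its absence here is not held against the trial. The rates above are chosen, and some of them leave the study arm ahead on any-cause events.

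What stands is the stated text. The one analysis sentence uses a narrower term than the endpoint sections, and cord harm is named only as radiation injury. On its ordinary reading that sentence filters a randomised comparison by cause, in a trial where cause may shift with the intervention.

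**Conclusion.** The point holds as a mismatch with a possible bias, not as a demonstrated one. The direction would favour local irradiation if two conditions are met: events are filtered by judged cause, and disease in the spared sectors produces some excess of events. The size cannot be derived from the article. Across the assumed rates, the restriction hides exactly the excess of unrelated events in the study arm, here 0 to 10 points. It removes the apparent advantage entirely once that excess equals the related-only gap. Significance would rarely be at stake at this sample size. The description of one arm as having fewer side effects could be.

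**What to change.** Reword the toxicity sentence in Statistical analysis and randomization so that the Fisher comparison, by randomised arm, covers vertebral fracture, spinal cord injury or compression, and nerve root compression at the treated vertebrae that are new or worse than on the planning CT, whatever the attributed cause. Count each patient once, since the Inclusion criteria allow up to three discontinuous vertebral metastases. Report radiation-related events as a descriptive subset. In the Measurement section, name cord compression of any cause next to radiation injury, so that both sections describe the same set of events.

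The cost is wording. Every patient already has a planning CT (Radiotherapy section), and CT of the vertebral bodies is already specified for these outcomes. The downside is that the difference in side effects may look smaller than in a related-only comparison.

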### Status

This trial was registered in the ChiCTR (NO: ChiCTR1900023401). The recruitment starts in January 2021 and is planned to be completed in two years.

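### Late side effects are compared by a Fisher exact test with no stated time point, so the rates depend on the data-cut date and on survival in each arm

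*Protocol article*

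**What the plan says.** The sections named here are all in the protocol article.

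- **Endpoint.** Objectives makes the incidence and types of side effects the secondary endpoint. Measurement of the primary and secondary endpoints counts cord injury from radiation and fracture among the imaging findings of interest. On how they are found, it says: "The vertebral bodies will be scanned with CT to identify radiogenic injury of the spinal cord and vertebral compression fracture".
- **Analysis.** Statistical analysis and randomization gives toxicity one sentence: "The related toxicity will analyze by Fisher exact test". It gives no time point and no treatment of death.
- **Follow-up.** The abstract describes long-term follow-up, in which "follow-up of patients will determine pain relief and side effects". Pain is assessed before radiotherapy and then "two weeks, three months, six months and every six months after radiotherapy". No last visit is given.
- **Entry and survival.** Under Status, "The recruitment starts in January 2021 and is planned to be completed in two years". Inclusion criteria require an estimated survival of at least three months.
- **Size.** "We estimate a loss to follow-up rate of 10% and the resultant required number of patients was 66". This calculation, with "α = 0.025, 1-β = 0.8", concerns pain relief. No figure is given for side effects.

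**The concern.** A Fisher test needs one yes or no per patient. With no stated time point, the natural count is whether the event was ever seen. A patient who dies at three months without a fracture then counts the same as one followed fracture-free for two years.

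Two things follow. The reported incidence rises as the data cut moves later, even if the underlying risk does not change. And an arm whose patients live longer has more time to show late events. The article expects the reduced target to give fewer side effects, so this comparison carries one of the trial's two main messages.

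**Working it through.** **Plan's own figure.** The only stated size is 66, or 66 / 2 = 33 per arm. The pain relief rates behind it are not given. Equal rates of about 0.955 would need 30 per arm, and 60 × 1.1 = 66, but other pairs of rates also give 66. It can be neither confirmed nor refuted, and nothing below depends on it beyond 33 per arm.

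**Assumptions.** The article gives no event rates, survival or cut date. I assume exponential fracture times (hazard h) and death times (hazard m), independent of each other, uniform entry over 24 months, a data cut a months after the last entry, no other loss, and two-sided 5% tests. A latent 12-month risk p means h = −ln(1 − p)/12. A median survival M means m = ln 2/M. Write s = h + m.

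**Step 1: the crude rate moves with the cut.**

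Cumulative incidence at time t with death competing: (h/s)(1 − e^(−st)).

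Expected crude proportion: (h/s){1 − [e^(−sa) − e^(−s(a+24))]/(24s)}.

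For p = 0.20 and M = 12: h = 0.0186, m = 0.0578, s = 0.0764, h/s = 0.2435. At 12 months, e^(−12s) = 0.8 × 0.5 = 0.40, so the cumulative incidence is 0.2435 × 0.60 = 14.6%, whatever the cut. The crude proportion is about 15.5%, 20% and 22.5% for a = 3, 12 and 24. With M = 6 the 12-month figure is 11.1%, and the crude proportion runs from about 11% to 14%.

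**Step 2: unequal survival, same fracture hazard.** Latent risk 30% in both arms, median survival 6 v 12 months, 10,000 simulated trials per row:

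| Cut after last entry | Crude rates | Fisher rejects | Log-rank rejects |
|---|---|---|---|
| 3 months | 16.8% v 23.1% | 5.7% | about 5% |
| 12 months | 19.4% v 29.0% | 8.5% | about 5% |
| 24 months | 20.1% v 32.4% | 13.2% | about 5% |

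The log-rank test is cause-specific, with death and end of follow-up censored.

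**Step 3: a real reduction hidden.** Latent risk 30% v 15%, with the lower-risk arm living longer (median 12 v 6 months). Fisher has 3% to 4% power over the three cuts, and the log-rank 22% to 28%.

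**Step 4: equal survival.** With p = 0.20 and M = 12 in both arms, Fisher's size is 2.0% to 2.5%. With follow-up of 3 to 27 months, death hazard 0.08 per month and fracture hazards 0.01 v 0.03 per month, power is about 20% for Fisher and 32% for the log-rank. A Pearson test on the same crude counts also gives 32%. For 30% v 10% latent risk and M = 12, over the three cuts:

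| Cut | Fisher | Pearson | Log-rank |
|---|---|---|---|
| 3 months | 27% | 42% | 42% |
| 12 months | 38% | 51% | 54% |
| 24 months | 41% | 54% | 58% |

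At the 24-month cut, 54 − 41 = 13 of the 58 − 41 = 17 points are Fisher's conservatism.

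**Step 5: what cumulative incidence does not remove.** Take fracture hazard 0.02 in both arms, death hazards 0.12 v 0.06 per month, and follow-up of 3 to 27 months. Crude rates are 11.6% v 16.3%. At 12 months the cumulative incidence is (0.02/0.14)(1 − e^(−1.68)) = 11.6% v (0.02/0.08)(1 − e^(−0.96)) = 15.4%. At six months it is 8.1% v 9.5%.

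**The case against.** A Fisher test on incidence is conventional for a secondary safety endpoint in phase II, and an article may leave the assessment time and the handling of death to the full protocol or SAP. The visit schedule is stated for pain, so applying it to side effects is inference, drawn from the abstract's description of follow-up and from the imaging sentences. This has weight: the full documents may fix a time point. But the article did not leave the method open. It names a test, and as described that test has no time point.

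Four stronger readings are tempting and do not hold.

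- **Staggered entry biases the comparison.** Allocation is randomised 1:1, so entry times balance on average. Bias between arms needs a survival difference. Both arms receive the same dose and no survival hypothesis is stated, so it would arise mainly by chance.
- **Ignoring event times is what costs power.** Step 4 shows that most or all of the gap is Fisher's conservatism.
- **Competing-risk incidence removes the survival effect.** Step 5 shows that it does not. It also falls in the arm that dies sooner, and Gray's test compares the same quantity. What it supplies is a defined time point.
- **False positives are inflated wherever survival differs.** At the Step 5 hazards Fisher rejects in only 3.9% of runs. Rejection passes 5% only with higher event rates or longer follow-up, as in Step 2.

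A six-month time point on its own would also be weak for late events. Under the hazards 0.01 v 0.03 of Step 4, a comparison at six months has about 24% power, below the 32% from Pearson on open-ended counts.

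**Conclusion.** The point holds in a limited form. As stated, the analysis gives late fracture and cord injury a crude incidence tied to no time; in the example it moves from about 15.5% to 22.5% with the cut date alone. If survival differs between arms, it can create a difference (Fisher rejection up to 13.2% under equal hazards) or hide one (3% to 4% power, against 22% to 28%). If survival is equal, the test is valid but conservative.

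The sizes rest wholly on assumed hazards, survival and cut dates, and on fracture and death being independent. The direction does not depend on the particular values. Acute effects and the primary pain comparison are not touched. It should be corrected, but it does not threaten the main conclusion.

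**What to change.** 1. For vertebral fracture and spinal cord injury, compare the arms by a cause-specific log-rank test, with death and end of follow-up censored.
2. Report cumulative incidence with death as a competing event at one pre-stated scheduled visit, for example 12 months, with six months as an early look. Give the arm difference, its 95% CI and the deaths by arm, so that a survival effect can be seen.
3. Do not list Gray's test as interchangeable with the log-rank, for the reason in Step 5.
4. Keep Fisher or simple proportions for acute effects, within a stated early window.

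If the full protocol or SAP already fixes a time point, cite it and align the wording.

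The cost is analysis wording and the use of event and death dates, which follow-up and adverse-event recording should already supply. The sample size and treatment do not change. A small downside is that event times found at visits are known only to the visit interval.
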